#### CBM-I training component

The first app-based CBM-I training session will take place in the lab, followed by four weeks (approx. five weekly sessions) of training from their homes or elsewhere. This will be an independent practice of what was learnt in the cognitive reappraisal component. The paradigm used for the CBM-I training is an adapted version of the Ambiguous Scenarios Task [84]. Participants are first presented with an ambiguous scenario. On the following screen, they are asked what thoughts they would have in this situation and are given two possible answers depicting a positive and a negative interpretation of the situation. Participants will be reinforced for choosing the positive solution. If participants choose the negative solution, they will be notified that there is a more helpful choice. This feedback will be provided in various formats. In line with previous research [85], a total of 500 scenarios will be delivered over four weeks. To better cater to the young sample, the 500 scenarios will be delivered over 20 sessions with 25 scenarios per session (rather than 10 sessions with 50 scenarios per session as in [85]), after receiving qualitative feedback that it was quite strenuous to complete all 50 scenarios. Furthermore, we chose to present the scenarios in text form, accompanied by matching, colourful images, again, to better cater to the young sample. The 500 ambiguous scenarios are appropriate for children in the target age range (10–14 years of age) and designed to capture depressogenic cognitive styles. If participants fail to complete the required sessions, they will be reminded of the importance of regular training via email. Participants will be notified that they are welcome to take breaks on their own terms, however, they should finish each session before the next one is scheduled. Participant will be provided with a training schedule to keep track of when the next session is scheduled.

##### Positive CBM-I condition

In line with previous research [85], in the positive CBM-I condition, 76% of the scenarios will be resolved positively, 12% will be resolved negatively and 12% will remain unresolved. Participants will receive feedback on the helpfulness of their response on all but the 12% of unresolved trials.

##### Placebo CBM-I condition

In the placebo CBM-I training the same scenarios will be presented as in the positive CBM-I condition. However, in 50% of the trials participants will not receive feedback on the helpfulness of their answer choices (no training). These items will be structurally identical to the 12% of unresolved trials in the positive CBM-I training. For the remaining 50% of items, participants will be presented with two answer choices based on factual elements of the scenario (rather than negative and positive interpretations of the scenario). These factual items will be followed by feedback on the accuracy of participants’ answer solutions. Participants in the placebo CBM-I training will be given access to the positive CBM-I training after study completion.

#### If–then plans component

The third component of the IB intervention are if–then plans (e.g., “if my friend is late to meet me at the park, then I won’t take it personally”). Participants will be provided with a colourful sheet where they can fill in each plan and a CoCo merchandise fridge magnet to hang up the sheet in their homes. If–then planning, also known as implementation intentions, reinforce the relationship between the expected situation and behaviour, so that when relevant cues appear, goal-relevant behaviour automatically occurs [86]. Thus, if–then plans reduce the gap between goal and action. A meta-analysis found if–then planning to be a successful tool for behaviour change in terms of achievements, relationships and health, with effect sizes (ES) ranging from medium to large [87]. Participants in the active and placebo conditions will receive differing instructions on the if–then plans. Participants in the active condition will be asked to complete weekly IB specific if–then plans, whereas participants in the control condition will be asked to complete non-interpretation bias specific if–then plans. Participants should make a commitment to take an action in a certain situation. An example if–then plan presented to participants in the active condition is, “if my friend doesn’t respond to my text message immediately, then I will interpret this as them likely being busy with other things.” An example if–then plan presented to participants in the placebo condition is, “if I’m in a rush on the way to school in the morning, then I will still wait for the traffic light to turn green.” The demonstrative if–then plan in the instructions for the placebo condition should be as neutral as possible, nevertheless, it is still possible that participants in the placebo condition create positive if–then plans, which could in turn influence certain outcomes. It is, however, less likely that they will create interpretation specific if–then plans, meaning the primary outcome measure of this study should not be affected.

### Measures

See Table 1 for screening and outcome measures as well as confounding variables.

#### Screening measures

The Diagnostic Interview for Mental Disorders (DIPS) [78] will be used to determine whether the parent of children in the HR sample meets inclusion criteria for a current or previous depressive episode (according to DSM-5 criteria) and whether both parents (if applicable) have no history of a disorder that would lead to exclusion from the study (bipolar disorder, psychosis or substance abuse). The DIPS [78] will also be used to establish the psychiatric diagnosis-free status of parents of children in the low-risk sample. The DIPS is a clinician-administered semi-structured interview used to identify both current and past psychiatric diagnoses in adults.

The Diagnostic Interview for Mental Disorders in Children and Adolescents (K-DIPS) [79] will be used to determine whether children have current or past psychiatric diagnosis according to DSM-5 criteria which would lead to exclusion of the study. The K-DIPS [79] is a clinician-administered semi-structured interview used to identify both current and past psychiatric diagnoses in children aged 6–18. Both the DIPS [78] and K-DIPS [79] will be conducted by team members trained in the use of the manual.

#### Outcome measures

The primary outcomes reflecting our hypotheses are IB, stress reactivity and stress recovery. Furthermore, as a secondary outcome measure, we will use Ecological Momentary Assessments (EMA) to sample participants’ current stress perception and stress coping mechanisms two times a week in a naturalist setting.

##### Interpretation bias

The first primary outcome measure is interpretation bias. This will be measured via a computerised version of the SST [30] adapted to encompass depressogenic stimuli. Two randomised versions (version A and version B) of the SST [30] will be administered pre (T1) and post (T2) IB intervention, with approximately four weeks between measurement timepoints. In the SST [30] participants are presented with 36 scrambled sentences containing six words each. They should use five of these words to build a sentence. Each word series contains more than one possible sentence formulation. Thirty of the scrambled sentences are emotional sentences (e.g., “total I winner a loser am”), with one positive and one negative sentence solution. The remaining six scrambled sentences are neutral sentences (e.g., “like watching funny I exciting movies”), with neutral solutions. IB represents the proportion of emotional sentences which were resolved negatively.

The scrambled sentences of version A of the SST were adopted from a previous study conducted by researchers involved in the present study [41]. The emotional sentences in version A are based on the original stimulus set developed by [88], were then translated into German [89], adapted and extended by researchers in the present research group [41]. Version B of the SST was created for the present study. Approximately 93% of the sentences in version B were adapted from version A of the SST, mainly by changing single elements such as the positive or negative valanced words. The remaining 7% of the sentences were directly adopted from a further study [90].

To avoid deliberate sentence building strategies, participants should complete a simultaneous cognitive load task [30]. Participants are presented with a four-digit number at the beginning of each of three blocks for 5,000 ms, which they should memorise and recall at the end of the block. The split-half reliability (odd vs. even trials) of version A of the SST was found to be acceptable (*r* = 0.53; *p* < 0.001) [41]. Version B was created to closely resemble version A.

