Outcome measures	Interpretation bias	SST (computer task)	T1, T2
	Physiological stress reactivity	Cortisol delta (via cortisol swabs at pre, 10 min post, 20 min post and 30 min post stressor)	T1, T2
	Physiological stress recovery	Cortisol levels at 45 min post stressor	T1, T2
	Subjective stress	SAM (self-reported change in current mood measured at pre, 10 min post, 20 min post, 30 min post and 45 min post stressor)	T1, T2
Confounding variables	Pubertal status	Tanner self-report and saliva sample	T1
	Depressive symptoms	R-CADS (self-report)	T1
	Anxiety symptoms	R-CADS (self-report)	T1
	Childhood trauma	CTQ (self-report)	T1

*CTQ* Childhood Trauma Questionnaire [77], *DIPS* Diagnostic Interview for Mental Disorders [78], *K-DIPS* Diagnostic Interview for Mental Disorders in Children and Adolescents [79], *R-CADS* Children’s Anxiety and Depression Scale [80], *SST* Scrambled Sentences Task [30], *SAM* Self-Assessment Manikin Scale [81]

Finally, after the four-week training period, HR individuals will be scheduled for a third session (T2). This post- intervention outcome assessment session will be structurally identical to the pre-intervention assessment at T1, with an adapted version of the TSST-C being administered as well as the version of the SST which they did not complete at T1.

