#### Hypothesis testing

To test the hypotheses that HR children have more negative IB (H1) and altered cortisol reactivity and recovery (H2, H3) when compared with LR children at T1, t-tests will be performed using IB, cortisol reactivity and recovery as dependant variables (DVs) and group membership (HR, LR) as the independent variable (IV). No specific predictions about the direction of effects for participants’ cortisol reactivity (H2) are made given the mixed literature [18]. For cortisol recovery (H3), it is predicted that HR participants’ cortisol levels will take longer to return to baseline after experiencing the laboratory stressor [47, 111]. Furthermore, to account for the possible confounding variables assessed in this study, a regression model will be run for the effect of group on IB, including age, depression and anxiety symptoms, childhood trauma, sex and pubertal status as covariates. The association between baseline IB and stress response will be looked at within each group (HR and LR) as well as in the entire sample using bivariate correlation. Bayes Factors will be calculated to warrant a rejection of the null hypothesis.

To determine whether the IB training was indeed more effective than the placebo training (H4) in HR individuals, a manipulation check will be conducted using ANOVA. In line with a previous study, participants who complete less than 80% of the training will be excluded from analyses [85].

To test the hypothesis, that the active (versus placebo) IB condition exerts effects on HR individuals’ stress reactivity and recovery (H5 and H6), an ANOVA will be conducted with the condition as the IV (active vs. placebo IB intervention) and cortisol reactivity and recovery as the DVs. Exploratory analyses will be conducted to determine the relationship between change in IB and change in stress response in HR individuals. All relevant confounding variables assessed in this study will be accounted for (age, symptoms of depression and anxiety, childhood trauma, sex, pubertal status, baseline cortisol response). Additionally, Bayes Factors will be calculated to determine whether the null hypothesis can be rejected.

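### SST version order is randomised and crossed, but no version or order term is named in the interpretation-bias analyses, so any A–B difference costs some precision

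*Protocol article*

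**What the plan says.** Interpretation bias (IB) is the first of the primary outcomes and is scored as the share of emotional sentences solved negatively. Under Interpretation bias the article says: "Two randomised versions (version A and version B) of the SST [30] will be administered pre (T1) and post (T2) IB intervention". The Procedure section (text after Table 1) adds that at T2 high-risk children complete "the version of the SST which they did not complete at T1". Order is therefore A then B for some children and B then A for others.

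The second version has no earlier history of use: "Version B of the SST was created for the present study". The article describes how close the two are meant to be. Its stated aim is that "Version B was created to closely resemble version A", and on the origin of the items it reports: "Approximately 93% of the sentences in version B were adapted from version A of the SST". The changes were to single elements, of which valenced words are given as an example. The only reliability figure (split-half r = 0.53) belongs to the older version: "The split-half reliability (odd vs. even trials) of version A of the SST was found to be acceptable".

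Under Hypothesis testing:
- H1 is a t-test of IB by risk group, followed by a regression with age, depressive and anxiety symptoms, trauma, sex and puberty as covariates.
- For H4, "a manipulation check will be conducted using ANOVA". No factors are named, not even time.
- The RCT paragraph lists the same confounders plus baseline cortisol response.

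Version or order appears in none of these.

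**The concern.** Version order is known for each child and set by randomisation. If one version draws more negative solutions than the other, each child's T2 minus T1 change carries that difference with a plus or minus sign depending on order. A model without an order term treats this explainable variation as noise.

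H4 tells the reader whether the training moved IB, and so how H5 and H6 are to be read. A null cortisol result means one thing if IB moved and another if the IB test was merely imprecise. The same noise would weaken the exploratory correlation between IB change and stress-response change.

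**Working it through.** **Inputs.** From Sample size: 50 per arm, 20% dropout, IB effect g = 0.52 to 0.70. Completers: 50 × 0.8 = 40 per arm. Not in the article and therefore assumed: the T1–T2 correlation r of IB (0.5 unless stated) and the A–B difference v in SD units of IB (shown as a range).

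**The plan's own figure.** The article has no power calculation for IB. Its N = 70 concerns the stress response. It reproduces as a group-by-time interaction with f = 0.34/2 = 0.17 and r = 0.5 (power 0.8007), and 70/0.8 = 87.5 gives 88. This does not bear on SST version, but it shows that r = 0.5 is consistent with the plan's own sizing.

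**Variance.** With half the children in each order, the change score gains +v or −v, which adds v² to its variance:

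- change score: 2(1 − r) becomes 2(1 − r) + v², an inflation of v²/(2(1 − r));
- single visit (H1 at T1, or T2 scores alone): 1 becomes 1 + v²/4. For H1 this takes the T1 version to be randomised in both risk groups.

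**Power for the change score.** Two-sample t-test, 40 per arm, noncentrality 0.52 × √(40/2) / √(2(1 − r) + v²). At r = 0.5 the numerator is 0.52 × 4.472 = 2.326.

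| v (SD) | Change variance, r = 0.5 | Change variance, r = 0.7 | Single-visit variance | Noncentrality (r = 0.5) | Power, no order term (r = 0.5) |
|---|---|---|---|---|---|
| 0 | – | – | – | 2.326 | 63.2% |
| 0.1 | +1% | +1.7% | +0.25% | 2.314 | 62.8% |
| 0.2 | +4% | +6.7% | +1% | 2.280 | 61.5% |
| 0.3 | +9% | +15% | +2.25% | 2.227 | 59.5% |
| 0.5 | +25% | +42% | +6.25% | 2.080 | 53.8% |

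In simulation (8,000 trials per setting, order assigned at random), power without the order term was 59% at v = 0.3 and 53% at v = 0.5. With the term it stayed at 62–63%. With baseline adjustment instead of a change score, power without the term was 75% at v = 0, 72% at 0.3 and 67% at 0.5, against 74% with it. At the upper cited effect of 0.70 the change-score figures are 87.1%, 85.8% and 84.2% at v = 0, 0.2 and 0.3.

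**Validity.** In a second simulation (4,000 runs per scenario) the estimated arm effect stayed at about 0.52 in every scenario. With simple randomisation of order and no order term, type I error was 4.2% at v = 0.3 and 5.0% at v = 0.5. With order balanced within arm and the term omitted, it fell to 2.6% at v = 0.5, so the test becomes conservative.

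**Chance imbalance.** Under simple randomisation the SD of the between-arm difference in the share starting with A is √(2 × 0.25/40) = 0.112. At v = 0.5 an imbalance of one SD moves the arm contrast by 2 × 0.5 × 0.112 = 0.11 SD. Over repeated trials this averages to zero and is covered by the standard error.

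**IB-change correlation.** At v = 0.5 and r = 0.5 it shrinks by the factor 1/√1.25 = 0.894, about 11%.

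**The case against.** The strongest case against has four parts.

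1. **Silence.** The H4 sentence names no factors at all, so it cannot show that version is left out. A condensed article may leave such a term to a fuller plan. A list of confounders is also not where one would look for a randomised design factor. This stands for H4. It does not remove the point for H1, where the t-test has risk group as its only factor and the regression covariates are listed by name.
2. **The design already protects the comparison.** Versions are randomised and crossed. This stands in full. A reader might infer that the arm comparison is biased, or that false positives rise. The documents do not support either reading, and the simulation contradicts both.
3. **The harm depends on an unknown.** A reader might infer from the new version B that the versions differ substantially. The article gives no difference and states that close resemblance was intended. Valenced words are only an example of what was changed. Up to v = 0.2 the loss is under 2 power points. Resemblance is asserted without data, but so would be a large difference.
4. **Scope.** The Background says the high-risk versus low-risk comparison is not part of the main RCT, and the IB-change analysis is labelled exploratory. Both are correct and limit the weight of the point.

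One counter-argument is weaker than it looks. With the interaction effect set at f = g/2, as in the sizing of N = 70, H4 power would be 99.6% and fall only to 98.4% at v = 0.5. An arm difference of g SD in change, with equal baselines, corresponds to f = g/4 = 0.13, which gives the 63% above. H4 therefore has little power to spare.

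**Conclusion.** The point holds as a matter of precision only. A factor that the trial randomises is absent from the listed covariates and unnamed in the H4 ANOVA, and any A–B difference then enters residual variance. The loss is negligible up to about v = 0.2, about 4 power points at v = 0.3 and about 9 at v = 0.5. These figures rest on 40 completers per arm, an effect of 0.52 SD, an assumed correlation of 0.5, equal use of the two orders and analysis of the change score. A higher correlation makes the relative variance inflation larger, and baseline adjustment makes the power loss somewhat smaller. At T1 alone the effect on H1 is slight. Severity is low: nothing in the plan is invalid, and the change costs almost nothing.

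**What to change.** - Prespecify SST version order (A then B, or B then A) as a fixed factor in the H4 model. In a change-score or baseline-adjusted model a main effect of order is enough. In an arm-by-time repeated-measures ANOVA, order must enter with its interaction with time, because a between-child main effect alone does not remove the version difference.
- Put the same factor in the exploratory analysis of IB change against stress-response change.
- Add T1 version to the H1 regression.
- Report the A–B difference in IB at T1, before any training, so that readers can judge equivalence.
- State how order is allocated, and whether it is balanced within arm.

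The cost is one degree of freedom per model. No new data should be needed, since giving the other version at T2 requires knowing which one each child had at T1. The term should be fixed in advance, because adding it after seeing a version difference would be a post hoc choice.

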##### Stress reactivity and recovery

Stress will be induced using the TSST-C [82]. The adult version (TSST) is the gold standard for inducing stress and reliably increases cortisol levels by two to four times [46]. The TSST-C [82] has been validated for children aged 8–14 years. In this task, participants are asked to finish a story and to solve a mental arithmetic problem (sequential subtraction) in front of an audience of two. Both tasks should last a duration of five minutes [82]. We were able to detect a significant change in cortisol from pre to 30- minutes post TSST-C in a small pilot study (*N* = 6), using the Wilcoxon Rank- Sum test (*Z* = 21, *p* = 0.028). See below for details on data processing and computation of cortisol response indicators.

Subjective stress response will also be assessed through participants’ change in current mood, using the 9-point affective valence scale of the Self-Assessment Manikin (SAM, [81]). SAM [81] is a pictorial scale, depicting a range of emotions from a smiling, happy figure to a frowning, unhappy figure. SAM has been found to be highly correlated with ratings obtained using more lengthy and verbal measures of subjects’ emotional response to an event and thus is a much more rapid yet effective instrument [91]. SAM will be administered immediately after each cortisol swab is taken, meaning the measurement timepoints [81] are the same as those for the saliva swabs; Pre-TSST-C [82], immediately post, 10 min post, 20 min post, 30 and 45 min post-TSST-C [82].

##### Ecological momentary assessment of stress

During the four-week app-based IB intervention, ecological momentary assessment (EMA) will be used to sample participants’ 1) stress on a given day, 2) how well they could cope with this stress and 3) if they were able to use the strategies learnt via the IB intervention to cope with stress. A questionnaire containing the above-mentioned questions will be sent to participants smartphones twice a week over a four-week period. EMA has several advantages over traditional pre- and post-measurement methods. One such advantage is the ecological validity it offers, as assessment takes place in real life situations rather than in the laboratory [92, 93]. Furthermore, EMA offers assessment of within-person variability across time, while individual characteristics are kept constant (e.g., sex, race/ ethnicity, and genotype) [94].

### Confounding variables

#### Pubertal status

Pubertal status has been found to be related to HPA axis activity, with cortisol levels increasing at later pubertal developmental stages [95]. Tanner’s Sexual Maturation Scale (SMS) [96, 97] will be used to assess participants pubertal status. According to a meta-analysis by Campisi et al. [98], a self-report of the Tanner Stages is suitable for reliably finding out whether the subjects are in an early or late pubertal stage. In the Tanner children are presented with a series of pictures depicting different pubertal developmental stages. Participants should select the image which best matches their stage of development. Differing versions will be given to boys and girls. An extremely high inter-rater reliability (100% for breast and 98% for pubic hair) was found in the comparison between a self-assessment by the subjects compared to a physical examination by trained nurses or paediatricians [99]. The self-reported developmental stage will be compared and validated with participants’ salivary hormone levels (estradiol, progesterone and testosterone), since these correlate positively with the Tanner Stages [100].

